##### Inclusion criteria

Patients who meet all the following inclusion criteria may be included in the clinical trial:Diagnostic criteria for severe or critical COVID-19Patients exhibiting positive etiological evidence of the SARS-CoV-2 nucleic acid determined using real-time polymerase chain reaction (PCR) or gene sequencing will be included. In addition, patients should meet at least one of the following diagnostic criteria of severe COVID-19. First, shortness of breath and a respiratory rate (RR) ≥ 30 times/min. Second, oxygen saturation (SpO_2_) in quiescent condition ≤ 93% using finger measurement. Third, arterial partial pressure of oxygen (PaO_2_)/oxygen inhalation concentration (FiO_2_) ≤ 300 mmHg (1 mmHg = 0.133 kPa). The PaO_2_/FiO_2_ will be recalculated when patients will be enrolled from regions at high altitudes, especially those located 1000 m above sea level, using the following formula: PaO_2_/FiO_2_ × [atmospheric pressure (mmHg) /760].The diagnostic criteria of critical COVID-19 should meet one of the following criteria, including respiratory failure and those who needed mechanical ventilation, shock, or respiratory failure combined with organ failure, which required monitoring and treatment in an intensive care unit (ICU).Diagnostic criteria for pulmonary fibrosisThe diagnosis criteria of pulmonary fibrosis will be in accordance with the guidelines of evidence-based medicine (2011 Edition) of the ATS, European Respiratory Society (ERS), Japanese Respiratory Society (JRS), and the Latin American Thoracic Association (ALAT).The inclusion criteria for patients with pulmonary fibrosis should meet one of the following conditions. First, subjects should present diffuse, asymmetric reticular formation in the lungs. Second, the reticular formation should show nodular shadows in a lung X-ray and there should be reticular shadows in the lower lobes of both lungs, especially under the pleura. Third, subjects should exhibit restrictive ventilation dysfunction, decreased lung volume, functional residual volume, and normal or increased forced lung volume (FLV)/ forced expiratory volume in 1 s(FEV1) upon assessing lung function. In addition, they should exhibit decreased carbon monoxide(CO) levels exhaled in the single-breath determination of CO. Open chest or thoracoscopic lung biopsy will be considered the “gold standard" for the diagnosis of pulmonary fibrosis.In this study, the pulmonary function indices must meet the following criteria. First, the predicted forced vital capacity (FVC%) must be between 50 and 90%. Second, the diffusion capacity for carbon monoxide (DLCO) should be between 30 and 90%. Third, the FEV1/forced vital capacity(FVC) must be over 80%. Fourth, when subject is at rest in a room and is respiring normally, the oxygen partial pressure should more than 50 mmHg.TCM syndrome differentiation for subjectsThe criterion of TCM syndrome differentiation complies with TCM disease diagnosis and efficacy standards promulgated by the China State Administration [32]. In addition, the criterion of Qi-Yin deficiency must meet the following criteria, including shortness of breath, cough, sputum expectoration, a small amount of yellow and white sputum, spontaneous sweating, night sweats, fatigue, drawl, dry mouth, afternoon hot flashes, hot facial flashes, anorexia, red tongue, thin white coating on the tongue, and weak pulse[32]. Qi-Yin deficiency was found to account for 41.5% (39/94) of all individuals with pulmonary fibrosis in other studies[33].Age: ≥ 18 yearsWritten informed consent must be obtained from the patient or from their legal guardian. Patient may also be enrolled upon confirmation of the urgency of participation in the clinical trial and the possible benefit to the patient assessed by an independent consultant, or the implementation of other established procedures to include patients who are unable to provide informed consent.

##### Exclusion criteria

Patients who meet any of the following exclusion criteria will be excluded from this trial. First, diagnosis of any lung diseases, such as bronchiectasis, tuberculosis, bronchial asthma, chronic obstructive pulmonary disease (COPD), dyspnea, respiratory failure, lung cancer, or those with a history of these diseases. Second, patients with a status of acute exacerbation of pulmonary fibrosis. Third, patients with severe disorders of the cardiovascular system, nervous system, and digestive system; serious mental diseases, tumors, human immunodeficiency virus (HIV) infection/acquired immune deficiency syndrome (AIDS), tuberculosis, autoimmune diseases, and severe liver and kidney dysfunction. Fourth, patients who received glucocorticoids, immunosuppressants, and other drugs for treatment of pulmonary fibrosis or other diseases in the past 3 months. Fifth, participation in another interventional clinical trial within the past 3 months. Sixth, patients who did not provide informed consent. Finally, lactating women will be excluded from the study.

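### The first exclusion criterion bars dyspnea and respiratory failure, past or present, with no exception for the COVID-19 illness and fibrosis that the inclusion criteria call for

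*Protocol article*

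**What the plan says.** Both eligibility lists are in the protocol article. Under Inclusion criteria, every condition must hold: "Patients who meet all the following inclusion criteria may be included in the clinical trial". Under Exclusion criteria, one condition is enough to remove a patient: "Patients who meet any of the following exclusion criteria will be excluded from this trial".

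The first exclusion opens with "First, diagnosis of any lung diseases, such as bronchiectasis" and its list of examples ends with "dyspnea, respiratory failure, lung cancer, or those with a history of these diseases". Nothing in it limits the rule to disease that preceded COVID-19, is unrelated to it, or is present at screening.

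The inclusion side has three relevant parts:

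- **COVID-19 severity.** For severe disease, "patients should meet at least one of the following diagnostic criteria of severe COVID-19"; the first of the three pairs shortness of breath with a raised respiratory rate. For critical disease, one of several conditions is needed, "including respiratory failure and those who needed mechanical ventilation, shock, or respiratory failure combined with organ failure".
- **Pulmonary fibrosis.** Required of every subject.
- **TCM syndrome.** Required of every subject: "the criterion of Qi-Yin deficiency must meet the following criteria, including shortness of breath, cough, sputum expectoration", followed by a longer list of features.

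Dyspnea is also recorded in enrolled subjects. It is among the clinical manifestations collected at enrolment and at each follow-up, and the Borg dyspnea score is a secondary outcome.

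**The concern.** The two lists pull against each other on features that define the target population. A site that applies the exclusion as written turns away people the trial exists to study: those left breathless, and those whose COVID-19 was critical because of respiratory failure. A site that sets it aside enrols patients who breach a written exclusion. Nothing in the article tells sites which course to take, so centres may reach different answers.

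At stake are whether 257 per group (514 in total, Sample size calculation) can be recruited, whether centres enrol the same kind of patient, and to whom the result applies. If breathless patients are turned away, the Borg score also has less room to improve.

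**Working it through.** No arithmetic applies beyond counting routes, and the plan gives no figure to reproduce. The check sets the two lists side by side.

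**Step 1. The combining rules.** Inclusion needs all conditions; exclusion needs any one. Any feature that inclusion demands of everyone and exclusion forbids leaves nobody eligible. Any feature that is only one way in removes the patients who came in that way.

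**Step 2. Each inclusion element against the first exclusion.**

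| Inclusion element | Demanded of everyone? | Met by the first exclusion? |
|---|---|---|
| Severe: shortness of breath with RR ≥ 30/min | No, 1 of 3 | Yes, through the history clause, if shortness of breath is dyspnea |
| Severe: SpO2 ≤ 93% | No, 1 of 3 | Not named |
| Severe: PaO2/FiO2 ≤ 300 mmHg | No, 1 of 3 | Not named |
| Critical: respiratory failure with mechanical ventilation | No, 1 of 3 | Yes, by name, through the history clause |
| Critical: shock | No, 1 of 3 | Not named |
| Critical: respiratory failure with organ failure, in ICU | No, 1 of 3 | Yes, by name, through the history clause |
| Qi-Yin deficiency, shortness of breath listed first | Yes, if the list is mandatory | Yes, if shortness of breath is dyspnea |
| Pulmonary fibrosis | Yes | Yes, if the words covering any lung disease are taken literally |

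Of the six COVID-19 routes, two collide with the exclusion by name. A third collides if shortness of breath is dyspnea (2 + 1 = 3). These are routes, not patients: the article does not say how many patients would enter by each, so no share of patients can be computed.

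**Step 3. What follows under each reading.**

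- *Strict.* Shortness of breath is dyspnea, and every Qi-Yin feature is mandatory. Then everyone who satisfies inclusion has dyspnea, everyone with dyspnea is excluded, and the eligible set is empty.
- *Intermediate.* Shortness of breath is dyspnea, but the Qi-Yin syndrome can be diagnosed without it. Then anyone breathless now or in the past is excluded, together with critical cases who had respiratory failure.
- *Narrow.* Dyspnea counts only as a separate diagnosis and not as a symptom. Respiratory failure is still named, and a history of it still excludes, so critical cases who qualified through it are lost.
- *Probable intent.* Only lung disease other than the index illness and its sequelae is excluded. The conflict disappears, but the text does not say this.

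**Step 4. Does another section settle it?** The Background describes severe COVID-19 as including respiratory failure and progressive dyspnea, and calls dyspnea a common manifestation of pulmonary fibrosis. Together with the recording of dyspnea during the trial, this indicates that such patients are wanted. It does not change the exclusion. Other sections blur the line further: the enrolment questionnaire collects COPD, tuberculosis and lung cancer, and Principles of data analysis lists other lung diseases as a confounder, although the first exclusion removes patients with these conditions.

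**The case against.** The strongest reply is that the intent can be recovered. The abstract and the aim describe patients recovered from severe or critical COVID-19 who now have fibrosis. The second exclusion removes only acute exacerbations of fibrosis, which would be redundant if fibrosis itself were barred. The first exclusion is framed as a list of diagnoses, whereas Qi-Yin shortness of breath is a feature of a syndrome. The Qi-Yin sentence introduces its list with *including* and rests on an external standard not shown here, so how many features are needed is not certain. A sensible site would read the rule as other lung disease.

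Much of this stands. It lowers the practical risk and makes the empty eligible set conditional. It does not remove the conflict: respiratory failure is a named exclusion, a history of it is enough, and no exception is written. Nor is this a detail left to a fuller document, since the criteria that are stated conflict with one another.

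A reader might also infer several stronger things that the article does not support:

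- *That inclusion requires respiratory failure.* It does not. It is one way to qualify; two severe criteria and the shock route name neither respiratory failure nor shortness of breath.
- *That a critical-disease stratum would be lost.* There is none; study centre is the stratification factor given under Randomization and blinding.
- *That the per-protocol set would be emptied.* The Database section names that set, but the article gives no membership rule, so this cannot be shown.
- *That the treatment comparison would be biased.* Allocation is 1:1 and stratified by centre. Differing eligibility readings change who is enrolled at a centre, but do not by themselves unbalance its arms.

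**Conclusion.** The concern holds as a contradiction between two operative rules. Followed as written, the first exclusion removes patients whom the inclusion criteria admit.

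Its size depends on the reading. Nobody is eligible on two assumptions together: that shortness of breath is dyspnea, and that the Qi-Yin list is mandatory, which is how "the criterion of Qi-Yin deficiency must meet the following criteria, including shortness of breath, cough" most naturally reads. An unconditional statement that no patient can qualify goes further than the text allows. The narrow reading drops both assumptions, and it still excludes critical cases who qualified through respiratory failure, two of the three critical routes. The missing exception for the fibrosis under study is a further drafting fault in the same sentence, though a site is unlikely to apply it literally.

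The consequences are for recruitment, consistency across centres and generalizability. The within-centre randomized comparison is not affected.

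**What to change.** Reconcile the Inclusion criteria and Exclusion criteria sections by amending the first exclusion criterion. It should state explicitly how each of these counts toward eligibility:

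1. dyspnea, given the Qi-Yin criterion and the Borg outcome;
2. respiratory failure during the index COVID-19 episode, and the period to which the history clause applies;
3. the pulmonary fibrosis under study, given that the opening words cover any lung disease.

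The test for the amended text is that it no longer removes patients whom the inclusion criteria admit. Which clinical rule to adopt is for the sponsor. If respiratory failure at screening is to remain an exclusion, it should be defined so that it fits the inclusion requirement of a resting oxygen partial pressure above 50 mmHg.

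The cost is a short eligibility amendment and notice to sites. It adds no procedures and leaves the sample size calculation unchanged.

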##### Drug preparation and treatment program

The treatment of pulmonary fibrosis will be in adherence to "The 2018 Diagnosis of Idiopathic Pulmonary Fibrosis Guidelines" as symptomatic treatment is indispensable for patients with pulmonary fibrosis [34–36]. Drugs including pirfenidone, acetylcysteine, and glucocorticoids, which have been proven to be efficacious in the treatment of pulmonary fibrosis will constitute the modern drugs in this study.

TCM herb granule 1 will be will be formulated as mixed granules for single TCM herb administration and packed in food-grade plastic bags (8 g/bag), the granules will comprise extracts of adenophora tetraphylla, radix glehniae, liriope graminifolia, codonopsis pilosula, selfheal, meretricis, angelica sinensis, arrowhead mushroom, oysters, seaweed, peach kernel, the root of red-rooted salvia, curcuma aromatica, rhizome sparganii, radices zedoariae, and radix astragali. TCM herb granules 2 is placebo and will be formulated using supplementary materials, and it will be packed in food-grade plastic bags (8 g/bag) (Table 1). The method of use of each drug is shown in Table 1.

**Table 1 Tab1:** Therapeutic regimen of this study

Drug	Dosage	Taking drug	Remarks
Pirfenidone	The initial dosage is 200 mg/time, 3 times/day; and then add the dose to 600 mg/time by 200 mg/day. Finally, the dose is 600 mg/time, 3 times/day for 12 months	Take it half an hour after breakfast, lunch and dinner, respectively	Drug must be used for each participant
Acetylcysteine	200 mg/time, 3 times/day for 12 months	Take it half an hour after breakfast, lunch and dinner, respectively	Selective use for all subjects
Glucocorticoid	0.5 mg × kg^−1^ × day^−1^ for 1 month, and then 0.25 mg × kg^−1^ × day^−1^ for 2 months, and then the dose decline to 0.125 mg × kg^−1^ × day^−1^ for 12 months	Take it half an hour after breakfast, lunch and dinner, respectively	Selective use for all subjects
Chinese medicine granules 1	8 g/bag, 2 bags/ time, 3 times/day for 12 months	Take this granula after mixing it with water, take it half an hour after breakfast, lunch and dinner, respectively	Drug must be used for each individual in treatment group
Chinese medicine granules 2	8 g/bag, 2 bags/time, 3 times/day for 12 months	Take this granula after mixing it with water, take it half an hour after breakfast, lunch and dinner, respectively	Drug must be used for each volunteer in control group

*kg* kilogram, *mg* milligram

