#### Safety indices

It is necessary to pay close attention to any changes in the relevant safety indicators during treatment as certain therapeutic drugs (especially herbs) may cause organ damage. The safety indices include body temperature, blood pressure, heart rate, respiration, height, and weight, among others[37] (Table 2). Upon and after recruitment, the safety indices of all subjects will be determined several times during the 12-month treatment procedure.

**Table 2 Tab2:** Safety indexes will be detected for each volunteer in the study

Classification	Index	Detection time point
Blood routine	Red blood cell, hemoglobin, white blood cell, white blood cell classification count, hematocrit, platelet, etc	When one volunteer will be recruited, these safe indexes will be detected for five times (0 month, 3rd month, 6th month, 9th month, 12th month) across whole study
Urine routine	PH, urine specific gravity, urobilinogen, urine blood, white blood cell, urine protein, glucose in urine, bilirubin, ketone body, urine red blood cell, etc	
Liver function	Total protein, globulin, albumin, alanine aminotransferase, aspartate aminotransferase, total bilirubin, direct bilirubin, indirect bilirubin, urine bilirubin, urobilinogen, serum bile acid, gamma glutamyltranspeptidase, alkaline phosphatase, etc	
Kidney function	Serum urea, uric acid, blood β-microglobulin, serum creatinine, etc	
Blood sugar	Fasting blood sugar	
Electrocardiogram	Chest leads, limb lead	

*PH* hydrogen ion concentration

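### The exclusion list bars lactating women but does not name pregnancy, so a pregnant woman who meets the other criteria is eligible as the article is written.

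*Protocol article*

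**What the plan says.** The section Exclusion criteria opens with the rule "Patients who meet any of the following exclusion criteria will be excluded from this trial". It then numbers its items from the first to the sixth and closes with "Finally, lactating women will be excluded from the study". The list carries no phrase that leaves room for further criteria.

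The section Inclusion criteria sets conditions on COVID-19 severity, pulmonary fibrosis, lung function, TCM syndrome, age and consent. The age condition is 18 years or over. Sex, pregnancy and contraception do not appear.

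Table 1 (Drug preparation and treatment program) makes pirfenidone compulsory for every participant for 12 months. The active granules are compulsory for the treatment group at "8 g/bag, 2 bags/ time, 3 times/day for 12 months"; the control group takes placebo granules on the same schedule.

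Table 2 (Safety indices) schedules laboratory tests at months 0, 3, 6, 9 and 12. Its urine row reads "PH, urine specific gravity, urobilinogen, urine blood, white blood cell, urine protein, glucose in urine, bilirubin, ketone body, urine red blood cell, etc". The accompanying text says "The safety indices include body temperature, blood pressure, heart rate, respiration, height, and weight, among others". No pregnancy test is named in either place.

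**The concern.** The authors considered reproductive status and placed it in the eligibility rules, but covered only one half of it. The list keeps out a woman whose infant could be exposed through milk, and is silent on a woman whose fetus would be exposed directly. An investigator who applies the printed criteria has no ground in them to refuse a pregnant candidate.

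What is at stake is an avoidable exposure of a third party to study drugs over as long as 12 months. The article itself treats the herbs with caution in the section Safety indices, where it notes that "certain therapeutic drugs (especially herbs) may cause organ damage". That remark explains why participants are monitored and says nothing about a fetus, but it shows that the authors do not regard the mixture as free of risk.

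**Working it through.** No formula decides this point. The check is whether any rule in the article keeps a pregnant woman out, followed by what she would be assigned if none does.

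**Step 1: the exclusion list, item by item** (Exclusion criteria).

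| Item | Subject | Covers pregnancy? |
|---|---|---|
| First | Other lung disease, present or past | No |
| Second | Acute exacerbation of fibrosis | No |
| Third | Severe organ-system disorders, mental disease, tumours, HIV, tuberculosis, autoimmune disease, severe liver or kidney dysfunction | No |
| Fourth | Glucocorticoids, immunosuppressants and other drugs in the past 3 months | No |
| Fifth | Another interventional trial in the past 3 months | No |
| Sixth | No informed consent | No |
| Last | Lactation | No |

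None of the seven items names pregnancy or covers it indirectly.

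**Step 2: the inclusion criteria.** All conditions concern disease, lung function, TCM syndrome, age and consent. A pregnant woman can meet every one of them.

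**Step 3: other places where a rule might stand.** The baseline questionnaire, the follow-up questionnaire, Table 2 and the three individual circumstances under Suspension of protocol do not name pregnancy. The article mentions pregnancy, contraception or a pregnancy test nowhere.

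**Step 4: the open and the closed lists.** The rows of Table 2 for blood, urine, liver and kidney end in an open phrase; the blood row, for example, is "Red blood cell, hemoglobin, white blood cell, white blood cell classification count, hematocrit, platelet, etc". The safety text is open-ended too. The exclusion list is not. So the article fixes eligibility in full, but does not fix the safety tests in full. The point rests on the former.

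**Step 5: what an enrolled pregnant woman would be assigned.**
- Pirfenidone: Table 1 gives a final dose of 600 mg three times a day for 12 months, 600 × 3 = 1,800 mg/day. This applies in both arms, so to all 257 + 257 = 514 planned participants.
- Active granules: treatment arm only, 257 of 514. Counting the named ingredients gives ten from adenophora to seaweed and six from peach kernel to astragalus, 10 + 6 = 16. The granule weight is 8 × 2 × 3 = 48 g/day, or 48 × 365 = 17,520 g (about 17.5 kg) over 12 months.

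The granule weight only describes the planned exposure; it is no evidence of harm.

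**The case against.** The strongest reply is that this is a journal article. Pregnancy testing, contraception and the reporting of pregnancies are commonly left to the full protocol, which is not shown. That reply stands for the tests: Table 2 is open-ended, so the absence of a named test does not show that none is planned. It does not stand for eligibility. The article prints the exclusion list to its last item and takes up reproductive status there, so the rule is stated and incomplete.

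A second reply is that no two passages contradict each other and that no estimand, error rate or analysis is affected. Both statements are true. The point is an omission in an eligibility rule that bears on safety.

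Three stronger readings are tempting, and the article does not support them.
- *A reader might infer that a woman who conceives would stay on all study drugs.* The section Therapeutic schedule says that dosage was not adjusted, and Dispensing the herbal medication says that the allocated regimen stays the same. Neither forbids stopping, and Participant withdrawal lets anyone leave at any time without giving reasons.
- *A reader might infer that a pregnancy would go undetected.* Participants are seen every 3 months, an independent safety board is in place, and the test lists are open. The article supports only the statement that it names no procedure for detecting pregnancy.
- *A reader might put a number on pregnancies during treatment.* If 10% to 20% of 514 participants could conceive and 1% to 4% of those did so within 12 months, the result would be 514 × 0.10 × 0.01 = 0.5 to 514 × 0.20 × 0.04 = 4.1. For the herb-exposed arm alone it would be 257 × 0.10 × 0.01 = 0.26 to 257 × 0.20 × 0.04 = 2.1. None of these rates comes from the article. The figures also count conceptions on treatment, whereas the gap in the exclusion list concerns women already pregnant at entry.

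**Conclusion.** The point holds for the exclusion list. As printed, a pregnant woman who meets the other criteria is eligible. She would be assigned 12 months of pirfenidone in either arm and, in the treatment arm, the 16-component granules as well.

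Its size in numbers of women cannot be derived from the article, and the conclusion does not need it: one such enrolment would be enough to matter, and the correction is very small. The conclusion assumes that the printed list is the list that sites apply. If the full protocol already excludes pregnancy, the article only needs to be brought into line with it.

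For a pregnancy that begins after enrolment, the conclusion is narrower: the article describes no procedure, and the relevant sections should be reconciled.

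**What to change.** 1. In Exclusion criteria, change the last item so that it excludes *pregnant or lactating women*.
2. Confirm pregnancy status at month 0 in women able to conceive, for example on the urine sample already collected for Table 2, and name that check in the table.
3. Reconcile Exclusion criteria, Table 2 and Suspension of protocol on a pregnancy that arises during the study. How it is handled clinically is for the sponsor to define and state; no rule is proposed here.

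The cost is one added term in the list, one inexpensive test on a sample already taken, and a negligible loss of recruitment. Sample size and analysis stay as they are.
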